#### Quantitative component of process evaluation

Information on key process variables will be collected from different stakeholders (Table 1). Data analysis will apply random-effect regression models and structural equation modelling including process variables as moderators or mediators of effect. Additional multivariate analyses will be carried out to analyse the effect of fidelity including dose (number, frequency and duration of peer support sessions), recorded by routinely administered monitoring and evaluation (M&E) forms, and implementation outcomes.

**Table 1 Tab1:** UPSIDES-RCT process measures

Variable	Scale	Number of items	Raters	Sample size total/per site	Timing^a^		
Measures as part of randomised controlled trial data assessments					t_0_	t_1_	t_2_
Experiences of peer support	Brief INSPIRE [51]	5	SU	279/47		x	x
Fidelity	UPSIDES peer support fidelity scale	32 25	SU PSW	279/47 60/10		x	
Other measures^a^					T_0_	T_1_	T_2_
Motivations, competencies and relationship characteristics	Recovery-oriented peer provider work-role model and prototype measure (ROPP) [52]	29	PSW	60/10	x	x	x
Empowerment	Empowerment Scale (ES) [31]	28	PSW	60/10	x	x	x
Recovery	Stages of Recovery (STORI-30) [33]	30	PSW	60/10	x	x	x
Recovery orientation	Recovery Self-Assessment (RSA) [53]	36	Mental health workers	30/5	x		x
		36	Key informants	12/2	x		x

*PSW* peer support worker, *SU* service user, *t*_*0*_ baseline, *t*_*1*_ 4 months, *t*_*2*_ 8 months

^a^Measurement points for other measures based on the entire duration of the intervention: T_0_ = baseline or earlier (at the start of the intervention); T_1_ = month 12 (intermediate); T_2_ = month 24 or earlier (at the end of the intervention)

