**Methods:**

UPSIDES-RCT is a pragmatic, parallel-group, multicentre, randomised controlled trial assessing the effectiveness of using peer support in developing empowering mental health services (UPSIDES) at four measurement points over 1 year (baseline, 4-, 8- and 12-month follow-up), with embedded process evaluation and cost-effectiveness analysis. Research will take place in a range of high-, middle- and low-income countries (Germany, UK, Israel, India, Uganda and Tanzania). The primary outcome is social inclusion of service users with severe mental illness (*N* = 558; *N* = 93 per site) at 8-month follow-up, measured with the Social Inclusion Scale. Secondary outcomes include empowerment (using the Empowerment Scale), hope (using the HOPE scale), recovery (using Stages of Recovery) and health and social functioning (using the Health of the Nations Outcome Scales). Mixed-methods process evaluation will investigate mediators and moderators of effect and the implementation experiences of four UPSIDES stakeholder groups (service users, peer support workers, mental health workers and policy makers). A cost-effectiveness analysis examining cost-utility and health budget impact will estimate the value for money of UPSIDES peer support.

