#### Statistical analysis and power calculation

Analyses will start once baseline data has been collected and cleaned. Descriptive statistics will be produced for all outcome measures, and outcome trajectories from t_0_ to t_3_ will be examined via exploratory analyses. The intervention’s effect on primary and secondary outcomes will be tested by means of random-effect regression models including a fixed group effect over time, allowing the inclusion of cases with incomplete (unbalanced) data across panels [36]. Post-hoc analyses will examine early (at t_1_) and late (at t_3_) effects for primary and secondary outcomes. All outcome analyses will be performed on an intention-to-treat basis. Per-protocol analyses will be part of the process evaluation (see below).

Sample size calculation was performed for testing whether the primary outcome (social inclusion) at t_2_ is affected by allocation. For six study sites, three time points, and estimated panel attrition of 10% at each time point, *N* = 558 participants (*N* = 93 per site) will be needed to detect a small effect size (0.25 SD units) with a power of 0.80 at a two-tailed significance level of 0.05. Sample size calculation was performed using the RMASS program (www.rmass.org) for a three-level mixed-effects linear regression model for the analysis of longitudinal data, assuming a linear effect over time, compound symmetry for error variance covariance, a person-level covariance (Int, Cov, Slope) of 0.300, 0.150, 0.100, and a centre-level covariance (Int, Cov, Slope) of 0.050, 0.025, 0.020.

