### Process evaluation

Participants in the process evaluation include service users, PSWs, mental health workers and other key informants involved in the UPSIDES intervention. PSWs and service users will be recruited from the participants in the randomised controlled trial (see above). Purposive sampling strategies will be applied for mental health workers and key informants. Mental health workers will be recruited from multidisciplinary teams who cooperate with PSWs. Key informants will be local stakeholders with relevant expertise relating to implementation of peer support work, including clinicians and managers who employ PSWs.

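### Process measures collected only in the intervention arm cannot moderate the randomised effect, and used as mediators they give only confounded within-arm associations

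*Protocol article*

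**What the plan says.** The abstract announces that "Mixed-methods process evaluation will investigate mediators and moderators of effect". The section on the quantitative component of the process evaluation gives the source of the variables, "Information on key process variables will be collected from different stakeholders (Table 1", and their role in random-effect regression and "structural equation modelling including process variables as moderators or mediators of effect". It then adds multivariate analyses of fidelity, including "dose (number, frequency and duration of peer support sessions), recorded by routinely administered monitoring and evaluation (M&E) forms", and of implementation outcomes.

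Table 1 lists:

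- **Service users (279 total / 47 per site):** Brief INSPIRE at t1 and t2; the fidelity scale at t1. Neither has a baseline value.
- **Peer support workers (60/10):** the fidelity scale at t1; the work-role measure, Empowerment Scale and STORI-30 on a separate calendar.
- **Mental health workers (30/5) and key informants (12/2):** the RSA, at the start and end of that calendar.

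The table's footnote defines that calendar after its starting point: "T_1_ = month 12 (intermediate); T_2_ = month 24 or earlier (at the end of the intervention".

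The intervention section gives UPSIDES peer support to the intervention group only; wait-list controls start after month 12. Allocation is 1:1 within site.

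**The concern.** A moderator of the trial effect is estimated from an interaction between arm and the variable, so the variable must have values in both arms. A mediator needs a path from allocation to the variable and a path from the variable to the outcome that is not merely shared prognosis. Ratings of a peer support relationship, ratings of its fidelity and counts of its sessions describe something that controls do not receive during follow-up.

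Given these roles, such variables would in practice produce correlations among intervention participants: those who are doing better may attend more and rate their peer worker more highly. Presented as moderation or mediation, those correlations could be read as evidence of how peer support works. The abstract's commitment on mediators and moderators would then rest on confounded associations.

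**Working it through.** **1. Whose data are the 279/47?** Inputs: N = 558 and 93 per site (sample size section), 1:1 allocation stratified by site (allocation section).

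- 558 / 2 = 279, as in Table 1.
- 93 / 2 = 46.5, shown as 47.

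The service-user process sample is exactly one arm. The content of the scales and the wait-list rule show that it is the intervention arm.

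**2. Moderation.** Let T be arm and M the process variable: Y = b0 + b1·T + b2·M + b3·T·M.

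- *Complete cases:* M is observed only where T = 1 (n = 279). The T column equals the intercept and T·M equals M. Rank is 2 of 4, so neither b1 nor b3 is estimable.
- *Controls coded M = 0:* T·M equals M everywhere. Rank is 3 of 4, so b3 still cannot be separated from b2.

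More participants would not change this.

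**3. Mediation.** With zero coding, Y = b0 + b1·T + b2·M has rank 3 of 3 and can be fitted, but b2 is learned only inside the intervention arm, where M was not randomised. Illustrative assumptions:

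- U is an unmeasured common cause with variance 1.
- In the intervention arm, M = 3 + 0.5·U + error (SD 0.866); M = 0 in controls.
- Y = 0.25·T + 0.5·U + error (SD 0.866), so M has no effect on Y.

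Expected results:

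- Var(M) in the intervention arm = 0.25 + 0.75 = 1, and Cov(M, Y) = 0.5 × 0.5 = 0.25, so b2 = 0.25 / 1 = 0.25 (truth 0).
- b1 = 0.25 - 0.25 × 3 = -0.50 (truth 0.25).

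A simulation of 500 trials of 558 gave mean b2 = 0.255 and b1 = -0.514. The apparent indirect effect is produced entirely by U. Its size depends on the assumed coefficients.

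**4. Site-level RSA as moderator.** Both arms exist at every site, so a baseline site score applies to both. The design with six site effects, T and T·RSA has rank 8 of 8, so moderation is estimable. Its precision, assuming outcome SD 1 and site RSA scaled to SD 1 (sum of squares 5 over six sites):

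- Variance of one site's arm difference = 4/n, plus between-site effect variance τ².
- SE of the moderation slope = √[(4/n + τ²)/5], tested on 6 - 2 = 4 df.
- n = 558/6 = 93, or 558 × 0.81 / 6 = 75.3 after two waves of 10% loss.

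| Total N | τ² | SE | Detectable at 80% power, two-sided 5% |
|---|---|---|---|
| 558 | 0 | 0.093 | 0.349 |
| 558 | 0.02 | 0.112 | 0.422 |
| 452 | 0 | 0.103 | 0.388 |
| 452 | 0.02 | 0.121 | 0.455 |

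These are in outcome SDs per SD of site RSA. All exceed the 0.25 SD main effect for which the trial is sized. Error in a site score from five staff or two informants is not included and would reduce precision further.

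**5. RSA as mediator.** The RSA is next taken at the end of the separate calendar, up to month 24, whereas the primary outcome is at month 8. A site score is also shared by both arms, so individual allocation within a site cannot move it.

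**The case against.** **Table 1 is not all one-arm.** A reader might infer that nothing in Table 1 can moderate anything. The documents do not support that. The RSA comes from staff and local stakeholders ("Mental health workers will be recruited from multidisciplinary teams who cooperate with PSWs") and describes the service in which both arms are randomised. Peer worker measures at the start, averaged by site, could be used in the same way. This stands, and limits the point to participant-level and participant-linked variables.

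**Mediation is not strictly unidentified.** UPSIDES dose is zero in controls by design, so there is a path from allocation to dose and a model can be fitted. This also stands. The defect in mediation is confounding, unlike the interaction, which cannot be estimated at all. A zero for Brief INSPIRE is less natural than a zero for sessions, because controls have no UPSIDES relationship to rate.

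**Timing.** A reader might argue that Brief INSPIRE is useless because its t2 value is taken at the primary-outcome visit. It is also taken at t1, before that visit, so timing alone does not exclude it.

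**The article does not give the models.** It does not say which variable has which role, and the separate fidelity and dose analyses, with per-protocol work placed in the process evaluation, are compatible with a within-arm approach. An analysis plan not shown may specify more. This stands for model detail, but no analysis plan can supply control-arm values that Table 1 does not collect.

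**Consequences.** The listed objectives do not name mediation or moderation; that commitment is in the abstract and the process evaluation section. It would be wrong to say that a listed objective fails.

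**Conclusion.** The point holds for Brief INSPIRE, fidelity, dose and peer worker measures linked to individual participants. They have no control-arm counterpart, so they cannot moderate the randomised contrast, and as mediators they yield only within-arm associations open to confounding. Site-level baseline measures are the exception for moderation: estimable, but over six sites with a detectable slope of about 0.35 to 0.46 SD per SD, under the assumptions shown. The RSA cannot act as a mediator.

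The conclusion on moderation rests only on the 279/47 counts and the wait-list rule. The size of the spurious mediation is illustrative. The primary analysis, the sample size and the secondary outcome comparisons are unaffected. This is a wrongly assigned analysis role in a supporting evaluation, and worth correcting before results are interpreted as mechanisms.

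**What to change.** In the section on the quantitative component of the process evaluation:

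- **Mediators:** constructs measured in service users of both arms at t1, for example the Empowerment Scale and HOPE, with SIS at t2 as outcome and t0 values of the mediator and SIS as covariates. Allocation to mediator is then a randomised comparison. Mediator to outcome is not, so state the assumption of no unmeasured mediator-outcome confounding.
- **Moderators:** t0 variables available in both arms, for example baseline SIS, TAG, diagnosis and site. Site-level baseline RSA may be added as exploratory only, with the six-site limit stated.
- **Brief INSPIRE at t1, fidelity and dose:** baseline-adjusted associations within the intervention arm, labelled non-causal.

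The cost is analysis wording. The Empowerment Scale and HOPE are already secondary outcomes, and the article already plans to examine these outcomes at t1. The downside is that Brief INSPIRE, fidelity and dose can no longer be reported as moderators or mediators of the trial effect.

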#### Qualitative component of process evaluation

The purpose of the qualitative component is to gain a deep multilayered contextual understanding of the impact and experiences of the UPSIDES peer support intervention among stakeholders. This component of the process evaluation includes four different qualitative studies, each focusing on a different target group: 1) service users’ experiences of the peer support intervention; 2) occupational development of PSWs; 3) practitioners’ experiences of peer support; and 4) key informants’ experiences of peer support.

A common overall methodology shared by each of these studies is described below and followed by detailed information on each of the individual studies. Table 2 gives an overview of qualitative studies which are part of the process evaluation.

**Table 2 Tab2:** Overview of qualitative studies

No.	Participants	Method	Sample size per site	Time point	
				T_0_	T_2_
1	Service users	Interviews	6–8		x
2	Peer support workers	Focus groups	2 groups (3–7)		x
3	Mental health workers	Focus groups	1 group (6–8)	x	x
4	Key informants	Focus groups	4–6	x	x

Measurement points for other measures based on the entire duration of the intervention: T_0_ = baseline or earlier (at the start of the intervention); T_2_ = month 24 or earlier (at the end of the intervention)

##### Overall methodology

Each study will follow the following steps: 1) provide verbal and written introduction to the study (participant information) and obtain written consent (consent form); 2) conduct and electronically record interviews or focus groups according to flexible topic guides; 3) collection of sociodemographic data; 4) transcribe audio recording verbatim and pseudonymise; 5) translate field notes and transcripts into English, if necessary; and 6) analyse data thematically through grouping and structuring of relevant themes to address key issues as per study objectives.

Data analysis will involve reviewing all field notes, reading and re-reading all the transcripts for familiarisation, consensual coding and generating themes. The data analysis will be conducted by a core group, supported by partners at each study site involved in data collection as needed. Data analysis will adhere to the following steps: 1) based on 1–2 interviews with participants, the task lead will develop preliminary codes and categories (themes); 2) preliminary codes and categories (themes) will be reviewed by the core group and commented on; 3) modifications of the coding tree will be commented on by the core group (the final coding tree will be discussed and revised as necessary until consensus is reached); 4) subsequent inclusion of interviews and modifications of sub-categories (themes); 5) reviewing, refining and defining themes; and 6) validation of the coding structure with each local site.

A code book will be developed using the data from all sites, which will then be shared across sites for review, discussion and standardisation. The pre-determined code book will be used to develop notes (data managed into units of information that cover broad categories with grouping of relevant emerging themes of importance). Each site will comment on the emerged themes, and the core analysis group will finalise the themes.

The study-specific core group will decide on the software to be used for data management and text retrieval (for example, QSR International’s NVivo 12 qualitative software, MAXQDA). The focus will be on the semantic content of the data (as responses to semi-structured questions). Quality will be improved by the use of multiple analysts to ensure that a range of perspectives informs the interpretation of the data; the use of verbatim quotes for each theme, to ensure the interpretation is as close to the data as possible; and local validation to maximise cross-cultural validity of the coding framework.

#### Service users’ experiences of peer support intervention

Objectives: In order to identify factors that contribute to the impact of peer support on service users, this study will explore service users’ views on positive/negative effects of peer support, and factors which moderate the positive/negative effects of peer support on social inclusion, (self) stigmatisation, empowerment, hope, recovery, and illness concepts. By using an open approach, the study will shed light on service users’ everyday experiences of the intervention beyond what is already known or expected regarding the mechanisms of impact, including active ingredients and conditions for optimal experiences as well as barriers and contextual influences.

Participants: Following a mixed-method approach, 6–8 service users from the intervention group at each site will be purposively selected at the end of intervention using their quantitative outcome data to include those with and without benefit (1:1) of peer support in terms of social inclusion and experiences of peer support. Participants will be selected based on their ratings on the SIS [30] and Brief INSPIRE [51] and grouped into ‘low responders’ (with a combination of low scores on the SIS and low scores on Brief INSPIRE) and ‘high responders’ (with a combination of high scores on the SIS and high scores on Brief INSPIRE).

Methods: Since an open approach allows for a deeper insight into personal systems of meaning among the interviewees [54], semi-structured interviews will be conducted at the end of the intervention to capture service users’ experiences with and subjective effects of peer support, and their attitudes towards peer support. Interviewers will use a flexible interview guide including 6–8 open questions to capture everyday experiences with peer support (for example, talks and activities), subjective appraisal of the positive/negative effects of peer support (for example, self-esteem, self-stigma and knowledge) and attitudes towards provision of peer support within mental health settings (for example, contextual factors, barriers and facilitators).

#### Peer support workers’ occupational development

Objective: To evaluate the impact of training and implementation on the occupational development of PSWs, to identify the views of PSWs on what contributes to or hinders successful implementation of peer support, and the attitudes of PSWs towards the benefits and challenges of the intervention. The study will address the gender-specific views of the PSWs on their occupational roles, facilitators and barriers, and resources and needs.

Participants: Two focus groups (one male, one female) per site with 3–7 participants in all six study sites, for 12 focus groups in total.

Methods: To allow for comparison, as well as to capture the diversity of PSW characteristics and activities across countries, focus group guidelines will include two parts. First, questions for PSWs across all sites focusing on: 1) experiences of PSWs and perspectives in their trained roles, including training and working as PSWs in this project; 2) the views of PSWs on personal benefit and challenges when using lived experiences in their role as a PSW; 3) the views of PSWs regarding effects on service users; and 4) barriers, facilitators and needs for successful implementation of peer support. Second, context-sensitive questions depending on a specific country’s stage of implementation and cultural characteristics focusing on obstacles and challenges of the PSW intervention at study sites. At study sites where the peer support model is new (for example, Ulm and Dar es Salaam), questions will focus on inner and outer setting factors relevant to the implementation of peer support (for example, local values and norms, power dynamics, organisational facilitators and barriers to implement peer support and to develop the occupational roles of PSWs). At study sites with more advanced implementation (for example, Be’er Sheva and Butabika), questions will focus on the experiences of PSWs in assimilation and sustainability of their role, benefits and challenges with the use of lived experiences (for example, self-disclosure and boundaries), and organisational facilitators and barriers to enhancing and sustaining peer support and to developing the occupational roles of PSWs (for example, financial arrangements).

#### Practitioners’ experiences of peer support

Objective: To investigate 1) the impact on the multidisciplinary team of PSWs joining and working in the team (“impact on team culture”); 2) the impact on the individual clinician of working alongside a PSW as a colleague (“impact on clinician”); 3) implementation issues that helped or hindered the successful implementation of PSWs in the team (“implementation”); and 4) the impact perceived by the clinician on service users who received peer support (“impact on service user”).

Participants: Mental health workers working in the same team as an UPSIDES PSW.

Methods: 6–8 mental health workers in each site will take part in a focus group before and after the intervention. A replacement clinician will be identified for follow-up if a baseline focus group attendee is no longer available (for example, because they have moved jobs). Purposive sampling will be used to maximise diversity in terms of age, gender and years since qualifying. Data will be collected using an open focus group guide based on an implementation scale developed through a previous systematic review [16]. This covers elements of organisational culture, training, role clarity, resourcing, access to a peer network and other factors essential for successful peer support implementation. In addition, at baseline and follow-up, focus group participants will be asked to complete a 16-item questionnaire (Mental Illness: Clinicians’ Attitudes Scale [55]) to assess changes of stigmatising attitudes towards people with mental illness after working with PSWs.

